### Process evaluation

Descriptive statistics will be used to characterise the study sample and to analyse the survey data of physicians and medical assistants according to intervention fidelity, e.g. adherence to different intervention components. Moreover, regression analysis will be used to gain information about the dependence between claims data based outcome measures and (a) the uptake and perceived impact of intervention components by participants, (b) the perceived impact of contextual factors, particularly those related to the practice networks, (c) perceptions of patients’ expectations regarding antibiotic prescribing.

The semi-structured interviews will be audio-taped and transcribed verbatim. The interview data will be qualitatively analysed using thematic framework analysis to classify and organise data according to key themes, concepts and predefined categories. The transcripts will be analysed and coded by researchers using qualitative data analysis software (e.g. Atlas.ti). Predefined categories of the framework of Flottorp et al. [23] will be used to identify determinants of practice regarding improvements in health professional practice concerning the appropriate use of antibiotics in acute non-complicated infections in ambulatory care.

Aims of the focus group discussions are (a) to understand opinions of the targeted groups of study participants, (b) to identify barriers in the implementation process and (c) to reflect consequences for a possible further development of the intervention. The duration of discussion per topic during the meetings will serve as parameter to identify key topics, main barriers and discussed solutions to overcome possible difficulties. Basis of this analysis will be structured manuals and audiotapes of each meeting.

Data triangulation will occur through an integrated approach where qualitative and quantitative data will be systematically incorporated. This will be done after all sets of data have already been analysed individually. This approach strengthens the analysis by taking a more holistic approach to analysing data and evaluating the study [24].

#### Patient survey

Descriptive statistics will be used to analyse the data collected through the patient survey. This will be done (a) in order to characterise the patient sample, (b) to show the frequencies of answers given to the questions (e.g. antibiotics expected vs. antibiotics received, information on antibiotics received, item response). Additionally, correlation and regression analysis will be done with data collected in the main surveys, e.g. in order to detect dependences between patients’ characteristics (age, sex, etc.) or their actual (index)-disease and patients’ experiences and expectations concerning antibiotic prescribing.

### Sample size calculation

The sample size calculation is based on the expectation to find an absolute reduction of the antibiotic prescription rate in targeted patients from 61 to 50% in intervention group A and from 61 to 45% in groups B and C. Thus, the effect is expected to be 5% higher in the enriched intervention groups B and C compared to intervention group A.

To control the overall type I error rate at 0.05 (two-sided), a hierarchical 3-step testing procedure will be applied. In the first step, the hypotheses of no difference between the pre- and post prescription rate in group B and C will be tested. If at least one of these hypotheses can be rejected, the hypothesis of no difference in the pre- and post rate in group A will be tested. If, additionally, this hypothesis can be rejected, the hypotheses of no difference between the post rates of groups A and B as well as groups B and C will be tested. The sample size is calculated based on chi-squared tests assuring a (global) power of 80% for the rejection of all the above described, hierarchically ordered hypotheses. Furthermore, to take the clustered structure into account, an intra-cluster correlation coefficient (ICC) for patients in practices of 0.05 and of 0.7 for cases clustered in patients is assumed. Together with the above described expected pre- and post prescription rates in the three groups, this results in a sample size of 23,933 patients in group A, 11,967 patients in group B and 11,967 patients in group C. With an average practice size of 80 patients per quarter this leads to 75 practices in group A, 38 practices in group B and 38 practices in group C.

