### Data analysis

#### Outcome evaluation

The primary objective of this study is to examine the change of the antibiotic prescription rate in targeted patients within three intervention arms and the comparison between the three intervention arms. The confirmatory analysis of the primary endpoint will be conducted on the basis of the Intention-To-Treat (ITT) population where all patients will be included in the analysis and assigned to the group they were randomised to.

To account for multiple testing and to assure a global significance level of 5%, a multiple test procedure for hierarchically ordered hypotheses will be applied. In the first stage, differences regarding the primary endpoint (prescription of antibiotics) before and after the intervention in intervention groups B and C are tested. To assure a significance level of 5% within the first level, the hypotheses for the pre- and post comparison will be tested at a local significance level of 5/2%. The second step includes the pre-and post comparison in intervention group A. The significance level of the rejected hypotheses from step one is taken (2.5% if only one hypothesis can be rejected, 5% if both hypotheses can be rejected). If significance is reached in intervention groups A and B, differences between groups A and B will be tested at a local significance level of 5/2%. Similarly, difference between groups A and C will be only tested if significance is reached for groups A and C in the steps 1 and 2. If the hypotheses in step 1 or 2 cannot be rejected, the group comparison will not be tested primarily.

In all stages described above, a logistic mixed effects model will be applied to assess the respective hypotheses regarding the primary endpoint. In the first and second stage, the time (before/after the intervention) is included as fixed effect. A random intercept will be included for patients and for practices. For the comparisons in the third stage, the intervention group will be included as fixed effect additionally. Furthermore, age and gender will be included as covariates. Finally, sensitivity analyses will be conducted using different populations (per protocol population where patients with major protocol violations are excluded and appropriate subgroups). Since all these analyses are based on claims data, missing values cannot be tracked.

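### The sample size section lists A vs B and B vs C as third-step tests where the analysis section lists A vs B and A vs C, and its 80% power to reject all hypotheses is unattainable as written

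*Protocol article*

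**What the plan says.** Two sections of the protocol article describe the same hierarchical procedure.

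- **Sample size calculation.** The procedure is introduced with "To control the overall type I error rate at 0.05 (two-sided), a hierarchical 3-step testing procedure will be applied". Step 1 tests pre vs post in B and in C. Step 2 tests pre vs post in A if at least one step 1 hypothesis is rejected. If A is also rejected, "the hypotheses of no difference between the post rates of groups A and B as well as groups B and C will be tested". No local levels are given here. The assumed rates go "from 61 to 50% in intervention group A and from 61 to 45% in groups B and C", and the size is described as "assuring a (global) power of 80% for the rejection of all the above described, hierarchically ordered hypotheses".
- **Data analysis, Outcome evaluation.** Steps 1 and 2 are the same pre/post tests, with local levels stated. In step 3, if A and B were both significant, "differences between groups A and B will be tested at a local significance level of 5/2"%. Likewise, "difference between groups A and C will be only tested if significance is reached for groups A and C in the steps 1 and 2". B vs C is not named.

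**The concern.** The two sections define different confirmatory families. One contains B vs C and omits A vs C; the other does the reverse. They also open step 3 differently. The sample size section opens both tests once A and at least one of B or C have been rejected. The analysis section opens each test only if A and the particular arm concerned have been rejected.

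The power statement is a second problem. A section that assumes equal rates in B and C cannot also promise 80% power for a set of rejections that includes B vs C. At stake is what the trial can claim about its between-arm comparisons: which of them are confirmatory, and how likely the trial is to detect them.

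**Working it through.** **Inputs from the article.** Post rates: A 50%, B 45%, C 45%. Overall alpha 0.05 two-sided; local level 2.5% in step 3 (analysis section). Chi-squared tests. ICC 0.05 for patients in practices and 0.7 for cases in patients. 80 patients per practice per quarter. Group sizes 23,933 / 11,967 / 11,967, in total 23,933 + 2 × 11,967 = 47,867.

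**Assumption not in the article.** Two cases per patient. The design effect formula is also a reconstruction.

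**1. Reproduce the stated size from 50% vs 45%.** Allocation 2:1, so k = n_B/n_A = 0.5.

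- Pooled rate = (0.50 + 0.5 × 0.45)/1.5 = 0.4833.
- n_A = [2.2414 × √(0.4833 × 0.5167 × 3) + 0.8416 × √(0.50 × 0.50 + 0.45 × 0.55/0.5)]² / 0.05² = (1.9400 + 0.7264)² / 0.0025 ≈ 2,844.0.
- Design effect = [1 + 79 × 0.05] × [1 + (2 − 1) × 0.7] = 4.95 × 1.7 = 8.415.
- A: 2,844.01 × 8.415 = 23,932.4, rounded up 23,933. B and C: half of that, 11,966.2, rounded up 11,967.

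The article's figures are matched. They come from one comparison of A with an enriched arm at local 2.5% and 80% power.

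**2. B vs C under the article's assumptions.** The difference is 45% − 45% = 0, so the rejection probability equals the test level at any sample size and any design effect. At the effective sizes 2,844 / 1,422 / 1,422 (2,000,000 simulated trials):

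| Local level | B vs C rejected | A vs B and B vs C both rejected |
|---|---|---|
| 2.5% | 2.47% | 1.5% |
| 5% | 4.95% | 3.5% |

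The stated power for the whole set is 80%.

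**3. The same claim with A vs C in place of B vs C.**

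- The two comparisons share arm A. Correlation of the two differences = (0.25/n_A) / (0.25/n_A + 0.2475/n_B); with n_A = 2n_B this is 0.25/(0.25 + 0.495) = 0.336.
- Standardised margin for each = (0.05 − 2.2414 × 0.01623)/0.01618 = 0.842, where 0.01623 and 0.01618 are the null and alternative standard errors. Power of each = 80.0%.
- Bivariate normal probability that both are rejected: 67.0% (simulation 67.0%). At least one: 80 + 80 − 67 = 93%.
- The pre/post tests do not limit this. Their power exceeds 99.9% at this design effect with each arm split equally before and after.

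**4. Sensitivity to cases per patient at the stated sizes.** One case (design effect 4.95): 96% per comparison, 93% jointly. Two (8.415): 80% and 67%. Three (4.95 × 2.4 = 11.88): 64% and 46%. Of these, only two cases per patient returns the stated sizes at 80%.

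**5. Type I error under the looser opening condition.** Suppose the analysis section's 2.5% levels are used. A sum of 0.025 + 2 × 0.025 = 0.075 would need C unchanged, A and B truly changed, and all post rates equal. With the assumed common 61% baseline, an unchanged C stays at 61% while a changed A or B does not, so neither B vs C nor A vs C can then be a true null. At most two 2.5% tests remain, giving 5%. Simulation over all post-rate combinations of 61/50/45% gave a maximum of about 5.0% with either pair.

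**The case against.** The strongest reply is that this is a one-letter slip. The 2:1:1 allocation makes A the larger shared comparator, the article says that "the effect is expected to be 5% higher in the enriched intervention groups B and C compared to intervention group A", no finite sample size could come from 45% vs 45%, and the stated sizes reproduce from A against an enriched arm. The analysis section is also the fuller text, and a detailed statistical analysis plan, not shown here, is promised before the final analysis.

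Most of this stands, and it rules out three stronger readings that a reader might infer:

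- *The trial was sized on B vs C, or really has about 2.5% power.* The numbers do not support this. The 2.5% describes the sentence as written, not the comparison behind the sample size.
- *The looser opening condition inflates the global error to 7.5%.* This joins one section's condition to the other section's local levels, a combination neither describes, and it needs unequal true baselines. With C at 45% throughout and A and B falling from 61% to 45%, simulation gives about 6.6% to 6.8%. Under the assumed common baseline, the error stays at about 5%.
- *The confirmatory test could be picked after seeing the data.* The analysis section sets out A vs B and A vs C with explicit conditions, so this goes too far.

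The slip does not explain everything. The opening conditions also differ, and the 80% statement remains wrong once the letter is corrected.

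**Conclusion.** The contradiction is real: the two sections differ on the second third-step comparison and on when step 3 opens. As written, the power to reject all hypotheses cannot exceed about 2.5% (5% if B vs C were tested at the full level), against a stated 80%. This conclusion needs only the assumed 45% in both arms.

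The likely intended pair is A vs B and A vs C. For that pair the stated sizes give about 80% power per comparison, about 67% for both and about 93% for at least one. These three figures rest on the reconstructed design effect, with two cases per patient, and on the whole stated group size entering the post-rate comparison, which is what reproduces the article's numbers. The defect lies in the stated hypotheses and the stated power. It does not show that the sample size was computed for the wrong comparison or that the 5% level is lost.

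**What to change.** In the Sample size calculation section:

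1. Replace B vs C with A vs C in the third step.
2. Adopt the analysis section's conditions (each comparison opened only if A and that arm are significant) and its local 2.5% levels.
3. Replace the 80% global power claim with about 80% for each of A vs B and A vs C, and about 67% for rejecting both under the stated assumptions. Give the design effect and the cases per patient used, so that the figure can be checked.

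The cost is one paragraph of text and one restated power figure; the sample size stays as it is. Only if the sponsor wants to keep a joint 80% claim would the size have to rise, to about 29,874 in A and 14,937 in each of B and C. That is about 59,750 in total instead of 47,867, under the same design effect and 2:1:1 allocation.

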## Discussion

The evidence base of large scale programs to reduce antibiotic prescribing in acute non-complicated infections in primary care is limited, so this project can provide an important contribution. Nevertheless, a number of limitations of the study should be acknowledged. The study is randomised, but the number of units for allocation (i.e. networks) is small, leaving room for bias. Primary and secondary outcomes are based on claims data, which have inherent limitations and strengths. Given the multifaceted programs, it will be difficult to separate out the impact of various program components. On the other hand, strong aspects of the program are its large scale and closeness to daily practice. The focus on practice networks and implementation outcomes, which will be explored in the process evaluation, adds value to the study. The analysis of components of the complex implementation programs, using the TIDier checklist, contributes to the transparency of the implementation programs.

## Abbreviations

AOK: Allgemeine Ortskrankenkasse (health insurer)
aQua: Institute for Applied Quality Improvement and Research in Health Care
CAP: Community-acquired pneumonia
CDSS: Computerised decision support system
DDD: Defined daily dose
DEGAM: German College of General Practitioners and Family Physicians
ESAC-Net: European Surveillance of Antimicrobial Consumption Network
FG: Fachgruppe (medical specialist group)
GP: General practitioner
ICC: Intra-cluster correlation coefficient
ICD: International Classification of Diagnosis
ITT: Intention-to-treat
P4P: Pay for performance
PP: Per protocol
SFTP: Simple FILE Transfer Protocol
SGB V: Social Code Book V, Germany
